### Study groups and randomization process

Consecutive patients on the waiting/referral list for PSVT ablations (referred to our tertiary center by other hospitals) will be screened for eligibility by dedicated study coordinators. When they meet the inclusion criteria, the patients will be enrolled in the study (as depicted in the flowchart for the study; see Fig. 1). After enrolment, patients will be allocated a unique study subject number in chronologically ascending order. Subsequently, they will be randomized to two treatment arms: the “CF-sensing” arm, ablation with a CF-sensing ablation catheter; and the “conventional” arm, standard ablation approach using a conventional (noncontact force-sensing) ablation catheter. Randomization will be performed by a computer-generated program (ALEA) based on a block randomization protocol using a block size factor of four. Randomization into the two treatment arms will be carried out with a 1:1 randomization ratio (50% probability for both treatment arms). The process of randomization will follow the general concepts of allocation concealment by incorporating the following prerequisites into the conduct of randomization: the EP specialists performing the ablation procedures do not have knowledge on the method of randomization utilized in the study; the EP specialists performing the ablation procedures do not keep a record of the results of randomization during previous ablation procedures; withdrawal from enrolment and randomization after the initial screening process and the subsequent EP study (that was positive for AVNRT or WPW-AVRT) must be explained thoroughly in the official clinical report by the treating specialist; the person in charge of the randomization process will not be the treating physician and neither will he/she be involved in the patient selection process; and the person in charge of the randomization will be contacted (over the telephone) by the treating specialist after the diagnostic part of the procedure has been completed. Stratification for study specific factors will not be conducted. The study will be performed in an open-label fashion: neither the patient nor the electrophysiologist (performing the procedure) will be blinded for the specific type of procedure.

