### Clinical follow-up procedure

Patients are discharged home within 2 days after the index procedure. Antiarrhythmic medication is discontinued after the ablation procedure. Follow-up of study patients is implemented as outlined in Table 2. All patients undergo physical examination, 12-lead ECG and echocardiography before and the next day after the procedure (note: only bedside echocardiography is performed after the procedure, in order to control for pericardial effusion). After discharge, patients have an outpatient visit at 3 months and at 12 months after the index procedure. During these outpatient visits, patients will be assessed for recurrence of palpitations (medical history), in addition to a physical examination and a 12-lead ECG. Additional outpatient visits during the 12-month follow-up period are scheduled only in the case of recurrence of symptoms (symptom-based follow-up appointments). In these cases, a detailed medical history and a 12-lead ECG will be taken, and the following additional examinations can also be performed (if necessary) in order to document the clinical arrhythmia: Holter monitoring (up to 3 weeks) and/or trans-telephonic event recorder (CardioMemo). In the case of recurrence, a redo electrophysiology study can be scheduled. An event qualifies as recurrence of clinical arrhythmia if the patient experiences identical complaints to those before the ablation procedure, and the same type of narrow-complex tachycardia is recorded with any of the following: 12-lead ECG, Holter monitor or trans-telephonic event recorder (CardioMemo). In addition, a recurrence is also identified in case the same type of clinical arrhythmia can be induced during a potential redo electrophysiology study, that was indicated due to recurrent palpitations. The occurrence of (serious) adverse events will be assessed and followed-up during the procedure, before discharge, and at 3 and 12 months post discharge (additional follow-up appointments can also be scheduled if necessary). Echocardiography is done in case follow-up of pericardial effusion/tamponade is necessary, chest X-ray is done to follow-up possible phrenic nerve damage and vascular ultrasound is done if vascular access complications require it.

**Table 2 Tab2:** Follow-up design of the COBRA-PATH study

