Type of clinical examination	Before the index procedure	1 day after the index procedure	3 months after the index procedure (outpatient visit)	12 months after the index procedure (outpatient visit)
Physical examination/history^a^	+	+	+	+
12-lead surface electrocardiogram^a^	+	+	+	+
Echocardiography	+	+ (bedside echo)	**–**	–
24-h (or longer-term) Holter monitoring^a^	If available	–	In case necessary to detect possible recurrence^b^	In case necessary to detect possible recurrence^b^
Trans-telephonic event recorder (CardioMemo)	If available	–	In case necessary to detect possible recurrence^b^	In case necessary to detect possible recurrence^b^

*COBRA-PATH* Contact-Force-Sensing-Based Radiofrequency Catheter Ablation in Paroxysmal Supraventricular Tachycardias

^a^These examinations can also be scheduled any time during the 12-month follow-up period in the case that the patient experiences recurrence of symptoms (symptom-based follow-up appointment)

^b^Decision to perform these examinations will be made jointly by the treating cardiologist and the study investigators

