### Statistical analysis

The number of radiofrequency applications during the ablation procedures of AVNRT and WPW-AVRT (primary study endpoints), as well as other continuous procedural parameters from the group of secondary study endpoints (such as total procedural duration, fluoroscopy time and overall duration of RF applications), will be expressed as mean ± SD or median (interquartile range) depending on their distributions, and statistical analysis of these variables will be conducted using either the two-sample *t* test or the Mann–Whitney test, again depending on the underlying distribution of the data.

The recurrence rate of PSVT at 1 year (as an indicator of long-term success rate of the index procedure), as well as the acute success rate and the major/minor complication rates of the index procedures (secondary study endpoints), will be presented as absolute and relative frequencies. The associations between treatment and these secondary endpoints will be analyzed with the chi-squared test or with Fischer’s exact test, as appropriate. Moreover, logistic regression will be performed to examine these associations and will, if needed, be adjusted for unbalanced baseline characteristics. Freedom from PSVT recurrence will be determined with Kaplan–Meier analysis, and differences in recurrence-free survival rates will be evaluated with the log-rank test. A *p* value of 0.05 will be considered significant for all statistical determinations, and all reported *p*-values will be based on two-sided tests.

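### Detection of one-year recurrence, a secondary endpoint, can differ between arms because rhythm recording and redo study are discretionary in an open-label trial

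*Protocol article*

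**What the plan says.** The protocol article, Statistical analysis, uses one-year recurrence as the measure of long-term procedural success: "The recurrence rate of PSVT at 1 year (as an indicator of long-term success rate of the index procedure". It is a secondary endpoint. It is compared between arms by chi-squared or Fisher's exact test, by logistic regression, and by Kaplan–Meier curves with a log-rank test.

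Clinical follow-up procedure gives two routes to a recurrence.

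- **Symptoms plus recording.** The patient has the same complaints as before ablation, and "the same type of narrow-complex tachycardia is recorded with any of the following: 12-lead ECG, Holter monitor or trans-telephonic event recorder".
- **Redo study.** "a recurrence is also identified in case the same type of clinical arrhythmia can be induced during a potential redo electrophysiology study", where that study was prompted by recurrent palpitations.

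Both routes involve discretion. Every patient has a history and a 12-lead ECG at 3 and 12 months, and an ECG is taken at any symptom-driven visit. Beyond that, "the following additional examinations can also be performed (if necessary) in order to document the clinical arrhythmia", meaning Holter monitoring and the event recorder. Footnote b of Table 2 says who chooses: "Decision to perform these examinations will be made jointly by the treating cardiologist and the study investigators". The redo study is optional too: "In the case of recurrence, a redo electrophysiology study can be scheduled".

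On blinding, Study groups and randomization process says that "neither the patient nor the electrophysiologist (performing the procedure) will be blinded for the specific type of procedure". No blinded assessor or adjudicator is described.

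**The concern.** Under the first route, documentation is part of the event. Two patients with the same symptoms can therefore be classified differently because one was given a recorder and the other was not. If people who may know the allocation make that choice case by case, the chance of being counted can differ between arms even when true recurrence is the same. The redo route does not close the gap, because it is also optional and starts from symptoms reported by unblinded patients.

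The authors also hold an expectation. The Discussion says that contact-force sensing should improve long-term as well as acute success.

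At stake is the only efficacy outcome measured after the procedure itself. It will have very few events, so its estimate is sensitive to one or two patients. The protocol states this monitoring rule outright, and no later analysis plan can recover recordings that were never made.

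**Working it through.** **The plan's own figures.** There is no sample size or power for recurrence. The only calculation is for the number of RF applications (Sample size calculation), and it sets the number of patients available here.

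- Difference on the log scale: 1.39 − 1.39 × 0.75 = 0.3475; SD 0.59; two-sided 5%; power 80%.
- n per arm = 2 × (1.960 + 0.842)² × 0.59² / 0.3475² ≈ 45.3, so 46 per arm and 92 in total, as stated.
- 92 × 1.15 ≈ 106, and 106 / 0.95 ≈ 112, as stated. That is 56 per arm randomised.

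**Expected recurrences.** The Background gives about 5% for AVNRT and 8% for WPW-AVRT with the conventional approach. Expected events per arm = n × rate.

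| Patients per arm | 5% | 8% |
|---|---|---|
| 46 | 2.3 | 3.7 |
| 56 | 2.8 | 4.5 |

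**Weight of one event.** With 56 per arm, one undocumented event moves that arm's rate by 1/56 = 1.8 percentage points and two move it by 2/56 = 3.6 points. The whole expected rate is 5–8%.

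**Hypothetical effect on the ratio.** The documents give no monitoring rates, so every probability below is an assumption. True recurrence is set equal in the two arms. If a patient is counted only when monitored, the observed ratio (CF-sensing / conventional) is the ratio of the monitoring probabilities.

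| Monitored, conventional | Monitored, CF-sensing | Observed ratio |
|---|---|---|
| 90% | 90% | 1.00 |
| 90% | 70% | 0.70 / 0.90 = 0.78 |
| 90% | 60% | 0.60 / 0.90 = 0.67 |

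If the imbalance ran the other way, the ratios would be 0.90 / 0.70 = 1.29 and 0.90 / 0.60 = 1.50.

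This model is too harsh, because an unmonitored patient may still be caught by a 12-lead ECG or a redo study. If that happens in 20% of them (also assumed):

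- 90% v 70%: (0.70 + 0.30 × 0.20) / (0.90 + 0.10 × 0.20) = 0.76 / 0.92 = 0.83.
- 90% v 60%: (0.60 + 0.40 × 0.20) / 0.92 = 0.68 / 0.92 = 0.74.

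The distortion shrinks but remains.

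**Effect on the test.** This uses 56 per arm, equal true recurrence, and Fisher's exact test at 0.05.

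| Documentation | Rejects at 5% true recurrence | Rejects at 8% true recurrence |
|---|---|---|
| 0.9 v 0.9 | 0.7% | 1.5% |
| 0.9 v 0.5 | 1.1% | 3.5% |
| 1.0 v 0.5 | 1.7% | 5.2% |

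For scale, 5 v 0 events gives p = 0.057 and 6 v 0 gives p = 0.027. Even a gap wider than those in the ratio table would seldom produce a significant result. The harm is to the estimate and to how a result of no difference is read.

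**The case against.** Several stronger readings are tempting, and the document does not support them.

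- **That recurrence counts only if a tachycardia is recorded in follow-up.** A reader might infer this from the first route alone. Induction at a redo study also counts. Being optional, that route reduces the problem without removing it.
- **That unblinded investigators decide alone.** The decision is joint with the treating cardiologist. The text names only the patient and the operating electrophysiologist as unblinded. That the decision-makers know the allocation is an inference from the open-label design and the absence of any blinded role.
- **That the plan implies a bias of 0.67–0.78.** Those ratios only restate assumed monitoring rates in one direction. Nothing in the document gives a gap or its sign, and equal monitoring is possible.
- **That a false positive is likely.** It is not, as the Fisher calculation shows. The Abstract already concedes that a significant gain in success rates may not be demonstrable.

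Other points also have force. Every patient has ECGs at 3 and 12 months. That a single ECG will seldom catch a paroxysmal arrhythmia is plausible, but the document does not say so. Requiring objective confirmation is sound in itself. The article condenses a fuller protocol, which may contain a criterion for when monitoring is necessary.

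What stands is narrower: the rule as published leaves the opportunity for documentation to case-by-case choice, without protection from knowledge of the arm.

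**Conclusion.** The point holds as a modest one. The published rule permits differential detection of one-year recurrence, and both the recording route and the redo-study route depend on discretion. The size and direction of any bias cannot be derived from the document.

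The firm part is the scarcity of events: about 2.3–4.5 per arm, given the document's 5–8% and 46–56 patients per arm. A handful of classification decisions will therefore shape the estimate. The ratios are illustrations and rest wholly on assumed monitoring probabilities. The number of RF applications, the primary endpoint, is not affected. This is a worthwhile improvement to a secondary endpoint, not a flaw that threatens the trial.

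**What to change.** 1. Keep the documented definition of recurrence as the main analysis.
2. Report by arm how many patients had recurrent palpitations, how many of those had Holter or event-recorder monitoring, and how many had a redo study. This shows whether the opportunity for detection was in fact similar.
3. Pre-specify a sensitivity analysis that counts every symptomatic recurrence, documented or not. State that it is open to reporting bias, since patients know their treatment; it complements the main analysis and does not correct it. Study population also admits patients with a manifest pathway who have never had palpitations. For them, count any new palpitations, because there are no earlier complaints to match.
4. For endpoint recording only, apply one arm-independent criterion for offering the recordings already listed in Table 2 to any patient who reports recurrent palpitations. Clinical decisions stay with the treating cardiologist.

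Item 1 changes nothing. Item 3 uses history already taken at the visits, and item 2 adds only a count of the recordings and redo studies done. Item 4 may add a few recordings in symptomatic patients, with equipment already in the plan. For patients already followed up without such a criterion, items 2 and 3 are what remains available.

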### Adverse events and safety monitoring

Adverse events are registered and reported according to regulations of the medical ethics committee. The occurrence of the following complications are considered a major (serious) adverse event: death, acute myocardial infarction/coronary artery damage, major bleeding, abdominal bleeding, cardiac tamponade or pericardial effusion requiring intervention (and/or prolonging the duration of hospitalization), ischemic cerebral event and other procedure-related embolic events, high-degree AV-block requiring PM implantation, atrial esophageal fistula, phrenic nerve palsy and vascular access complications (requiring intervention and/or prolonging the duration of hospitalization, e.g. arteriovenous fistula, or aneurysm). Minor adverse events are as follows: mild pericardial effusion, minor bleeding, and minor vascular access complications that do not require interventions and do not prolong the duration of hospitalization; in addition, nonsustained high-degree AV-block or sustained first-degree AV-block not requiring pacemaker implantation.

Since the conduct of this trial is considered low risk for participating subjects (due to the fact that CF-sensing catheters have already been proven by multiple clinical studies to be safe in the ablation of other types of cardiac arrhythmias), the ethical committee has agreed to omit the establishment of a safety committee.

### Statistical analysis

The number of radiofrequency applications during the ablation procedures of AVNRT and WPW-AVRT (primary study endpoints), as well as other continuous procedural parameters from the group of secondary study endpoints (such as total procedural duration, fluoroscopy time and overall duration of RF applications), will be expressed as mean ± SD or median (interquartile range) depending on their distributions, and statistical analysis of these variables will be conducted using either the two-sample *t* test or the Mann–Whitney test, again depending on the underlying distribution of the data.

The recurrence rate of PSVT at 1 year (as an indicator of long-term success rate of the index procedure), as well as the acute success rate and the major/minor complication rates of the index procedures (secondary study endpoints), will be presented as absolute and relative frequencies. The associations between treatment and these secondary endpoints will be analyzed with the chi-squared test or with Fischer’s exact test, as appropriate. Moreover, logistic regression will be performed to examine these associations and will, if needed, be adjusted for unbalanced baseline characteristics. Freedom from PSVT recurrence will be determined with Kaplan–Meier analysis, and differences in recurrence-free survival rates will be evaluated with the log-rank test. A *p* value of 0.05 will be considered significant for all statistical determinations, and all reported *p*-values will be based on two-sided tests.

### Sample size calculation

The sample size calculations were based on the following:
A retrospective analysis of AVNRT/WPW-AVRT ablations performed in our institute within the last 6 months revealed that the mean number of radiofrequency applications required for successful ablations was 4.81 ± 3.21, which is in line with previous results found in the literature [30].According to previous studies, the ablation efficiency for patients with atrial fibrillation has been increased with the use of CF-sensing technology by approximately 15–20% [1, 4–19], as revealed by the reduced number and duration of RF applications in atrial fibrillation ablation. We assume that in terms of ablation efficiency, the significance of CF sensing will be even more pronounced in the treatment (catheter ablation) of such simple arrhythmia substrates as that of AVNRT and WPW-AVRT, therefore (regarding our sample calculations) a 25% reduction in RF application number was considered realistic to represent a clinically significant change.

Evaluation of the distribution of RF applications in our database of AVNRT/WPW-AVRT ablations (mentioned under the first point) revealed a positive skewness, and therefore logarithm transformation (natural log) was performed in order to approximate a normal distribution of the variables. The mean and standard deviation of the natural logs of application numbers were computed and amounted to 1.39 ± 0.59; these values were subsequently used in our sample size calculations.

For the sample size calculations, we used two different calculator tools: an online sample-size calculator tool (http://powerandsamplesize.com/Calculators/Compare-2-Means/2-Sample-Equality) and G*power (http://www.gpower.hhu.de/en.html). In both methods, we applied the appropriate test comparing the difference of two independent means of two groups (calculation formulas are presented on the calculator’s website and in G*power). The mean application number of the group with the study catheter was assumed to be reduced by 25% (as already mentioned) compared to the control group (thus amounting to 1.39 × 0.75 = 1.043) and the standard deviation of this group was assumed to be identical to the control group. The power was set to 80% and the type 1 error (α) to 5% (two-tailed). Using these parameters, both methods/calculators determined the same sample size of patients (2 × 46 = 92), which would be required to show a statistical significance in the case of a clinically significant reduction (25%, as mentioned earlier) of RF application number.

Allowing a dropout rate of 15%, the total sample size would become around 106. In addition, the acute success rate of AVNRT/WPW-AVRT ablations has been reported to be around 95% [26, 29]. Taking this into consideration, the total number of patients required for the purposes of this study would be 112.

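### The 25% reduction was applied to the mean of the logs, so 92 patients have 80% power for a 29.4% reduction but only about 64% for the stated 25%

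*Protocol article*

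**What the plan says.** All of this is in the Sample size calculation section of the protocol article.

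- The target is stated in words on the count scale: "a 25% reduction in RF application number was considered realistic to represent a clinically significant change".
- Because the institution's counts were positively skewed, they were log-transformed: "The mean and standard deviation of the natural logs of application numbers were computed and amounted to 1.39 ± 0.59". The section says these values were carried into the calculation.
- The mean in the contact-force arm was obtained by multiplying the log mean by 0.75, "thus amounting to 1.39 × 0.75 = 1.043", and is described as a mean application number reduced by 25%. For the spread, "the standard deviation of this group was assumed to be identical to the control group".
- With 80% power and a two-sided 5% level, the result is 2 × 46 = 92 patients. The section says this number is needed to show significance "in the case of a clinically significant reduction (25%, as mentioned earlier) of RF application number".
- The total is then raised to about 106 for 15% dropout and to 112 for a 95% acute success rate.

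**The concern.** The value 1.39 is the mean of the logarithms, not a number of applications. Multiplying it by 0.75 does not reduce the count by 25%. A percentage change in a count becomes an addition or subtraction on the log scale, and its size does not depend on the baseline. The step taken does depend on it: multiplying the log mean by 0.75 is a 16% reduction from a geometric mean of 2, 29% from 4 and 44% from 10.

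At the baseline given, the effect entered into the calculators is larger than the effect stated in words. The 80% power therefore belongs to an effect that the protocol does not name, and the power for the effect that it does name is lower. This is the primary endpoint and the trial's main claim of superiority. A reader who trusts the stated power could take a non-significant result as stronger evidence against a 25% reduction than it is.

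**Working it through.** **Inputs** (Sample size calculation, except the allocation ratio)

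- Control log mean 1.39; log SD 0.59 in both arms
- Log mean used for the contact-force arm: 1.39 × 0.75 = 1.0425, printed as 1.043
- Target in words: 25% fewer RF applications
- Two-sided alpha 0.05 (z = 1.960); power 80% (z = 0.842)
- Allocation 1:1 (Study groups and randomization process)

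**Step 1: reproduce the plan's figure.** The formula is n per arm = 2 × [SD × (1.960 + 0.842) / shift]².

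- Shift used: 1.39 × 0.25 = 0.3475; standardised, 0.3475/0.59 = 0.589
- n = 2 × (0.59 × 2.802/0.3475)² = 45.3, so 46 per arm and 92 in total

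This matches the plan, so there is no doubt which calculation was run. With the noncentral t distribution, 46 per arm give 79.8% power at this shift.

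**Step 2: what that shift means for the count.**

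- exp(1.39) = 4.01 and exp(1.0425) = 2.84
- exp(-0.3475) = 0.706, a 29.4% reduction (29.3% from the rounded 1.043)

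**Step 3: the shift that matches 25%.**

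- ln(0.75) = -0.2877, so the log mean becomes 1.39 - 0.288 = 1.102 and the geometric mean goes from 4.01 to 3.01
- Standardised: 0.2877/0.59 = 0.488

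**Step 4: power and sample size for a true 25% reduction.**

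| Analysed per arm | Normal approximation | Noncentral t |
|---|---|---|
| 46 (92 in total) | 64.7% | 63.8% |
| 56 (112 in total) | 73.2% | 72.5% |

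- n for 80% power = 2 × (0.59 × 2.802/0.2877)² = 66.03, so 67 per arm (134); with the t distribution, 68 per arm (136)
- With losses of 15% and then 5%: 134/0.85/0.95 = 165.9 and 136/0.85/0.95 = 168.4, so 166 to 169 enrolled

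**Step 5: smaller effects.** The protocol cites efficiency gains of 15 to 20% from atrial fibrillation studies. At 46 per arm, a 15% reduction (shift 0.163) has about 26% power and a 20% reduction (shift 0.223) about 43%, by noncentral t.

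**Step 6: does the scale rescue the figure?** It does not.

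- A lognormal distribution with log mean 1.39 and log SD 0.59 has mean exp(1.39 + 0.59²/2) = 4.78 and SD 3.08, close to the reported 4.81 ± 3.21. With equal log SDs, the ratio of arithmetic means equals the ratio of geometric means, so reading the 25% as a change in the arithmetic mean gives the same shift.
- A t test on untransformed counts (difference 0.25 × 4.81 = 1.20, SD 3.21) would have only about 43 to 44% power at 46 per arm.

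**Step 7: the inflation to 112.**

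- The plan's 106 matches 92 × 1.15 = 105.8, and 106/0.95 = 111.6 gives 112
- Keeping 92 after both losses needs 92/0.85/0.95 = 113.9, so 114; conversely, 112 × 0.85 × 0.95 = 90.4, so about 90 remain

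**The case against.** The error itself is hard to dispute: the section's closing sentence speaks of the RF application number, so the 25% cannot be read as a change in the log mean. The case on the other side is about size and weight.

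- **The 64% may be the low end.** RF applications are counted during the index procedure, and randomisation takes place in that same procedure, after the diagnostic part. Patients lost during the 12-month follow-up would still have a primary outcome, and the exclusion section does not list acute failures as such. More than 92 could be analysed. This stands, so both figures should be given: about 64% at 92 and about 72% at 112. Neither reaches 80%.
- **The planned test may differ.** The Statistical analysis section names a t test or a Mann–Whitney test according to distribution and does not mention logs. The figures are therefore approximate for the final analysis. If the Mann–Whitney test is assumed to have 0.955 relative efficiency, power at 46 per arm is about 63%.
- **Inflated totals depend on the method.** With the plan's own arithmetic (× 1.15, then / 0.95), 134 to 136 evaluable patients become about 162 to 165, not 166 to 169. This is fair, but it changes little.
- **The 114 against 112 is minor.** It is: 45 instead of 46 per arm lowers power for a 25% reduction by about one percentage point, to 62.8%. The arithmetic is still right, and it is corrected in the same section.
- **Nothing is biased.** A sample-size error leaves the type 1 error and the estimate untouched. That is true. What is wrong is the statement of what the trial can detect, and the remark on misreading a null result is a caution about interpretation.

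**Conclusion.** The concern holds, and the section must be corrected, because its power statement for the primary endpoint is wrong as written. The calculation has 80% power for a 29.4% reduction, not for the stated 25%. For 25%, power is about 64% with 92 evaluable patients, a miss rate of about 36% instead of 20%. If all 112 are analysed it is about 72%, a miss rate of about 28%. Reaching 80% would take 134 to 136 evaluable patients, nearly half as many again as 92.

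These figures rest on the protocol's own inputs (log SD 0.59 in both arms, two-sided 5%, 1:1 allocation) and on comparing log means with a t test.

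**What to change.** In the Sample size calculation section, replace the multiplication of the log mean by a log difference of ln(0.75) = -0.288, giving a contact-force log mean of 1.102. Keep the 112 patients and restate what they provide, using one method throughout. By noncentral t:

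- 92 evaluable patients give 80% power for a reduction of about 29% (29.4%) in the number of RF applications and about 64% for 25%
- if all 112 are analysed, power for 25% is about 72%

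In the same section, correct the inflation: 92/0.85/0.95 = 114, and 112 enrolled leave about 90 evaluable under the stated losses.

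The cost is a rewording of this section and a less favourable stated power. It needs no extra patients and no change to trial conduct.

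### The 15% dropout allowance is applied as 92 × 1.15 = 106 instead of 92/0.85 = 109, so at the plan's own loss rates 112 patients leave about 90 evaluable, not 92; the effect on power is about one percentage point

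*Protocol article*

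**What the plan says.** All of this is in the protocol article, section Sample size calculation, unless noted.

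- Control-arm input: "The mean and standard deviation of the natural logs of application numbers were computed and amounted to 1.39 ± 0.59".
- Study-arm mean: the control log mean is reduced by a quarter, "thus amounting to 1.39 × 0.75 = 1.043"; for the spread, "the standard deviation of this group was assumed to be identical to the control group".
- Error rates: "The power was set to 80% and the type 1 error (α) to 5% (two-tailed").
- Result: "both methods/calculators determined the same sample size of patients (2 × 46 = 92"). The tools were an online two-means calculator and G*Power. The article does not say whether either run was a z or a t calculation.
- First allowance: "Allowing a dropout rate of 15%, the total sample size would become around 106".
- Second allowance: an acute success rate of about 95% is taken into account, after which "the total number of patients required for the purposes of this study would be 112". No formula is given for either allowance.
- Allocation, from Study groups and randomization process: "Randomization into the two treatment arms will be carried out with a 1:1 randomization ratio".
- Under Statistical analysis, the primary endpoint is to be compared by a two-sample t test or a Mann–Whitney test.

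**The concern.** A dropout rate is a share of the patients who enter. To finish with 92 when 15% of entrants are lost, one divides by 0.85. Multiplying by 1.15 gives too small a number, because the 15% then comes off the larger total. The figure 106 is exactly what the multiplication gives, and it carries through to the final 112.

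What is at stake is whether the enrolment figure and the stated 80% power belong together. A reader who takes 112, removes the two losses that the plan names and expects to get back to 92 will not get there.

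**Working it through.** **Inputs.** Log-scale means 1.39 and 1.043, so the difference is 0.347 (0.3475 if 1.39 × 0.25 is left unrounded); common SD 0.59; two-sided 5%; 80% power; 1:1 allocation; 15% dropout; 95% acute success. All are from the article.

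**Step 1: reproduce 46 per arm.** Normal approximation: n per arm = 2 × [SD × (1.960 + 0.842)/difference]².
- Difference 0.347: 45.4, rounded up to 46.
- Difference 0.3475: 45.3, rounded up to 46.

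The stated 2 × 46 = 92 is reproduced.

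**Step 2: the same inputs by exact (noncentral) t.** The standardised difference is 0.347/0.59 = 0.588 (0.589 unrounded).
- 46 per arm: 79.7 to 79.8% power.
- 47 per arm: 80.6 to 80.7% power.

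A t-based run on the printed inputs therefore returns 47. If the study-arm mean was entered as 1.04 (difference 0.35), 46 per arm gives 80.4%, and a t-based run also returns 46.

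**Step 3: the dropout step.**
- Multiplication: 92 × 1.15 = 105.8, or 106. This is the stated figure.
- Division: 92/0.85 = 108.2, or 109.
- Check on 106: 106 × 0.85 = 90.1, below 92. Put the other way, 106 covers a loss of (106 − 92)/106 = 13.2%, not 15%.

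**Step 4: the acute-success step.** 106/0.95 = 111.6, or 112. But 106 × 1.05 = 111.3 also rounds up to 112, so the final figure does not show which operation was used.

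**Step 5: what 112 leaves.**

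| Losses removed | Evaluable | Power, exact t | Power, normal approximation |
|---|---|---|---|
| 15% and 5% | 112 × 0.85 × 0.95 = 90.4 | 79.0 to 79.1% | 79.9 to 80.0% |
| the same, rounded down to 45 per arm | 90 | 78.8 to 78.9% | 79.7 to 79.8% |
| 15% only | 112 × 0.85 = 95.2 | 81.1 to 81.2% | 81.8 to 82.0% |

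Ranges run from a difference of 0.347 to 0.3475.

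**Step 6: division throughout.** From 92: 92/0.85/0.95 = 113.9, or 114; check 114 × 0.85 × 0.95 = 92.1. From 94 (47 per arm): 94/0.85/0.95 = 116.4, or 117, and 118 for equal arms.

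**The case against.** The best defence is that the shortfall depends on convention and on a pessimistic count of losses.

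- **Normal approximation.** Under the method that reproduces 46, the 90.4 remaining patients still have 79.9 to 80.0% power. This stands.
- **Acute failures.** The primary outcome is the number of radiofrequency applications in the procedure, and a failed ablation has that count too. The section on excluding enrolled patients from follow-up does not list acute failure alone as a reason. If these patients are analysed, about 95 remain and the target is met. This stands as well. Against it, the plan itself adds patients for the 95% success rate, and its baseline count is for successful ablations, so its own accounting treats failures as lost.
- **Timing of dropout.** Randomisation follows the diagnostic part of the procedure and the endpoint is counted in the same session, so later loss to follow-up cannot remove it. Only exclusions such as a catheter not introduced, or a switch to an incompatible catheter before acute success, can. The latter may overlap with the 5%, so taking both losses in full is close to a worst case. It is still the plan's own allowance.
- **Wording.** The article says around 106. That does not rescue the step, since 106 is the rounded output of 92 × 1.15.

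Three stronger readings are tempting, and the article does not support them.

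- A reader might infer that the two allowances contradict each other, one multiplied and one divided. No formula is stated, and 106 × 1.05 also leads to 112.
- A reader might infer that 46 per arm is wrong and that the two tools cannot have agreed. The normal approximation gives 46, and neither the G*Power routine nor the exact entries are stated.
- A reader might infer that 112 leaves the trial underpowered for its own assumption. That needs exact t, the full 15% and the full 5% together, and even then the gap is about one point.

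**Conclusion.** The dropout step is wrong on its own terms: 106 should be 109. This does not depend on which test or software was used. With both of the plan's allowances, 112 enrolled patients leave about 90 evaluable instead of 92.

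The size is minor: two patients at enrolment (114 against 112), and about 79% power by a t-based calculation or about 80% by the normal approximation. If acute failures are kept in the primary analysis there is no shortfall. Starting from 47 per arm would widen the enrolment gap to 5 or 6 patients, but whether 46 needs correcting depends on settings that the article does not report.

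These power figures hold only for the printed log-scale difference of 0.347 and SD of 0.59. They are not power for a 25% reduction in the number of applications. Taking a quarter off the mean of the logs corresponds to a reduction of about 29% in the geometric mean (1 − e^−0.347 = 0.293). A 25% reduction would be −ln 0.75 = 0.288 on the log scale, for which 46 per arm gives only about 64% power (exact t). That is a separate matter, but it limits how the restated power may be described.

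**What to change.** Choose one of two corrections in Sample size calculation:

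1. Keep 112. Restate it as about 90 evaluable patients after both allowances, with about 79% power (t-based) for a log-scale difference of 0.347 and SD of 0.59. This costs no patients, only a slightly less favourable power statement.
2. Show the derivation by division, 92/0.85/0.95 = 114. This costs two patients.

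With either option:

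- Write out the formula for each allowance.
- Say whether patients with acute failure are counted in the primary analysis. If they are, the second allowance is not needed, and 112 leaves about 95.
- State which routine (z or t) and which entries gave 46 per arm. Correct the statement that both tools agreed only if the G*Power run was t-based on 1.39, 1.043 and 0.59. In that case start from 94, which leads to 117, or 118 for equal arms.
- Tie the restated power to the log-scale difference actually used, and do not describe it as power for a 25% reduction in application number.
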